# Functional brain activation changes associated with practice in delaying smoking among moderate to heavy smokers: study protocol and rationale of a randomized trial (COPE)

**DOI:** 10.1186/s13063-018-2984-x

**Published:** 2018-11-12

**Keywords:** Smoking, Functional magnetic resonance imaging, Randomized trial, Study protocol

## Abstract

**Background:**

Most smokers struggle to overcome tobacco addiction. Neuroscientific models of addiction emphasize the importance of brain regions associated with cognitive control and reward to understand the cycle of addiction and relapse. During an attempt at abstinence, the cognitive control system appears to be underpowered to override the heightened reward system of the addicted brain. Thus, one neural target for treatment is to strengthen the cognitive control system. It may be possible to improve the functioning of the cognitive control system via deliberate practice.

**Methods/design:**

This study will determine the effects of practicing delaying smoking on brain and behavioral measures of cognitive control. Smoking patterns will be monitored for 1 week and then smokers (*N* = 80) will be randomized to either practice cognitive control by delaying their first cigarette of the day for 2 weeks (practice group) or they will continue monitoring only (no practice group). Functional magnetic resonance imaging will be performed while smokers regulate their responses to smoking images (i) at baseline and (ii) after 2 weeks of practice (or no practice).

**Discussion:**

The primary aim of this study will be to identify the impact of practicing cognitive control on functional brain activation changes in response to smoking cues. If successful, this project will establish a neurobiological biomarker for increasing cognitive control and demonstrate the feasibility of neuroimaging methods to predict the efficacy of an intervention without a large clinical trial.

**Trial Registration:**

ClinicalTrials.gov, NCT03080844. Registered March 15, 2017

**Electronic supplementary material:**

The online version of this article (10.1186/s13063-018-2984-x) contains supplementary material, which is available to authorized users.

## Background

Thirty-six million American adults smoke cigarettes [1] despite the known negative consequences [2]: nicotine addiction is difficult to overcome. Dual-system models of addiction assert primary roles for two systems: the cognitive control network (dorsolateral (dlPFC), dorsomedial, and ventrolateral prefrontal cortices [3–5]) and the reward network (ventromedial (vmPFC) and medial prefrontal cortices, and striatal regions [3–5]). In addiction, the cognitive control network is considered underactive while the reward network is considered overactive [3–6], resulting in a reward network that overrides the cognitive control network leading to relapse during quit attempts [4, 5, 7, 8].

An important implication of these models is that pharmacotherapy and/or behavioral treatments for smoking cessation should ideally target both systems to improve outcomes [4, 5]. There is evidence that bupropion and varenicline reduce activation in the reward network [9–12], but there is little evidence for any interventions that impact the cognitive control network. Cognitive-behavioral smoking cessation treatment commonly involves identifying and altering smoking cues (triggers), self-monitoring, and cognitive restructuring [13]. In clinical practice, smokers are encouraged to develop a quit plan whereby they self-administer these techniques to resist cravings and maintain abstinence [13, 14]. Counseling patients to use these techniques after they quit significantly improves cessation rates [15]; however, it is unclear whether using these techniques impacts either the cognitive control or reward networks.

Although the neural impact of behavioral cessation treatment is unknown, evidence from research on cognitive behavioral therapy (CBT) for depression indicates that practicing behavioral strategies can impact cognitive control areas [16, 17]. This suggests that cognitive control *practice* could enhance smokers’ ability to resist cravings and improve success at maintaining abstinence. If true, this would have important treatment implications because current behavioral treatment does not routinely implement practicing behavioral strategies *prior* to making a quit attempt. Emphasizing cognitive control practice prior to quitting could theoretically improve the effectiveness of cessation by enhancing smokers’ cognitive control capacity.

The purpose of this study is to examine among smokers the effect of cognitive control practice on cognitive control brain activation during efforts to regulate craving. Brain activation can be measured non-invasively using functional magnetic resonance imaging (fMRI) while smokers view smoking cues or images that trigger cravings [18–21]. Greater efforts to regulate craving (i.e., exerting cognitive control) have been linked to greater activation of the dlPFC [15], which is implicated in the cognitive control network [14]. In this study, participants will be randomized to 2 weeks of practice in exerting cognitive control by delaying the first cigarette of the day or smoking as usual; the comparison group will monitor their smoking behavior but will not be asked to delay smoking cigarettes. This study will identify whether: (i) cognitive control practice leads to changes in brain activation, (ii) associations exist between the amount of practice and brain activation changes, and (iii) individual differences in practice relate to brain activation changes. This will enhance our understanding of treatment mechanisms and provide a model for studying the impact of behavioral interventions on brain function.

### Study objectives

#### Primary objective

The primary objective is to identify the impact of practicing compared to not practicing delaying smoking on functional brain activation changes in the cognitive control networks in response to smoking cues. We hypothesize that practice vs. no practice will lead to greater brain activation increases in the cognitive control network when comparing pre- to post-intervention.

#### Secondary objective

In the group practicing delaying smoking, the secondary objective is to examine the association between the amount of practice (i.e., the amount of time the first cigarette of the day is delayed) and functional brain activation changes in the cognitive control network in response to smoking cues. We hypothesize that greater levels of practice will correspond to greater brain activation increases in the cognitive control network when comparing pre- to post-intervention.

#### Other objectives

Additional objectives are to examine the association between practice-related brain activation changes in the cognitive control network and individual differences (e.g., nicotine dependence, motivation, and sex). We hypothesize that practice-related increases in brain activation in the cognitive control network are expected to be greatest among more dependent and less motivated smokers as well as women.

## Methods/design

### Study overview

We will use a randomized design (parallel group, two-arm, superiority trial with a 1:1 allocation ratio) to examine the impact of practicing delaying the first cigarette of the day on cognitive control brain networks during an fMRI cue-reactivity task (see Fig. 1). Smokers (*N* = 80) will receive tips on how to resist the urge and control cravings to smoke and then be randomized either to practice progressively delaying their first cigarette of the day over a 2-week period (practice) or not to practice delaying their first cigarette and smoke as usual over a 2-week period (no practice). Portable carbon monoxide (CO) monitors will be used to assess objectively the timing of the first and second cigarettes of the day (days 1–7) and subsequently to monitor practice adherence (i.e., the delay of the first cigarette of the day; days 8–21). All participants will be given brief advice on techniques to help them control urges to smoke based on cognitive behavioral therapy (CBT) techniques. Participants will continue monitoring their smoking behavior regardless of group assignment. At baseline (day 7) and following 2 weeks of practice (day 21), participants in both arms will complete an fMRI session during which they view smoking and food cues and are asked to rate how much they want them. All study procedures will be conducted in accordance with the Code of Ethics of the World Medical Association (Declaration of Helsinki) and have been approved by the Institutional Review Board of the University of Kansas (protocol STUDY00004095). This experiment is registered at ClinicalTrials.gov (NCT03080844).

**Fig. 1 Fig1:**
[figure not shown]
Flow chart of enrollment, interventions, and assessments

### Design justification

Our reason for delaying the first cigarette of the day as a way to operationalize practice is based on theoretical and practical considerations. The first cigarette of the day is typically one of the most preferred cigarettes of the day, as smokers replenish nicotine levels depleted during sleep. Time to first cigarette of the day is also used as a proxy for level of nicotine dependence [22]. This cigarette is, therefore, an ideal clinical target for practicing skills for remaining abstinent. It also provides a practical way to standardize practice in a way that all participants can implement and it is simple to assess practice duration. We limited the practice duration to 2 weeks and fMRI assessments to 2, to avoid undue participant burden and to constrain the resources needed for the project within reasonable limits.

Careful consideration was given to the selection of the fMRI task for the proposed study. We selected the smoking cue-reactivity task based on findings supporting robust activations in cognitive control regions (particularly the dlPFC) [23] and based on a wide body of previous neuroimaging studies of smoking showing that cue reactivity can activate the cognitive control networks [18–21, 24].

#### Analysis plan

The planned data analyses are built around three specific aims. The first aim is to compare changes in brain activation in cognitive control regions as a result of cognitive control practice. The second aim is to determine the effect of adherence to the practice regimen on changes in brain activation in cognitive control regions. The third aim is to explore the effects of individual differences (e.g., level of tobacco dependence, motivation, and sex) on changes in brain activation in cognitive control regions.

##### Aim 1

Our primary aim is to identify the impact of practicing delaying the first cigarette of the day compared to not practicing on functional brain activation changes in cognitive control regions. The percentage signal change when comparing the negative smoke condition to the positive smoke condition will be computed for our a priori cognitive control region of interest (ROI) (i.e., dlPFC) for each subject at each time point and entered into a two-way mixed-effects ANOVA model using the group (practice, no practice) × time (pre, post) interaction. We hypothesize that practice vs. no practice will lead to greater pre-to-post brain activation *increases* in the cognitive control network.

##### Aim 2

We will also identify the impact of *adherence* to practicing delaying cigarettes on functional brain activation changes in the cognitive control networks in response to smoking cues. Using only participants from the practice group, we will calculate Pearson correlations between differences in brain activation from the negative smoke and positive smoke conditions and amount of practice completed. Brain activation will be computed as percentage signal change from pre- to post-treatment in response to smoking cues in the a priori dlPFC ROI. Practice will be quantified as the proportion of time delayed from their usual first cigarette of the day to their second cigarette of the day and subjectively measured by participants’ perceived difficulty in delaying the first cigarette of the day. We hypothesize that greater levels of practice will show greater brain activation increases in the cognitive control network in response to negative smoke compared to positive smoke conditions from pre- to post-intervention.

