#### Power and sample size

The sample size was based on aim 1 and calculated based on changes in brain activation observed in pilot data following 1 week of practicing CBT skills and 2 weeks of CBT sessions. Assuming the no practice group will have a mean of 0 change in brain activation between day 7 and day 21, and equal variance in the two groups, our preliminary data suggest Cohen’s *d* effect sizes of 2.77 and 3.70 for dlPFC and vmPFC, respectively. These effect sizes suggest *n* = 5 and 4 subjects per group are required to achieve 80% power at 0.05/2 = 0.025 significance level (Bonferroni correction needed to compensate for tests involving each of two brain regions) in a two-sided two-sample *t*-test. However, the small sample in our pilot data (*N* = 6) also indicates wide 95% confidence intervals. Using the conservative estimates of the lower bound of the mean and upper bound of the standard deviation, the effect sizes are (0.0991/0.1415) = 0.70 and (0.2037/0.1889) = 1.08. Using a sample size of *n* = 40 per group provides 79% and > 99% power for dlPFC and vmPFC, respectively; the power will be greater if the actual effect sizes are larger than the conservative estimates.

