#### Randomization and blinding

Following the brief counseling, participants will be randomized using a 1:1 allocation ratio to the practice or no practice arm of the study. Groups will be stratified on gender and marijuana use to prevent these variables from confounding treatment effects. Based on previous recruitment data, we expect a 1:1 ratio of men to women and a 1:2 ratio of marijuana users to non-marijuana users. Separate blocked randomization sequences (www.randomization.com) for each of the four strata will be used. A person from outside the study team, who will have no interaction with the participants or the data, will generate the sequence and reveal the group assignments prior to building the practice schedule. Staff responsible for enrolling subjects will not participate in generating the randomization sequence and will not have specific knowledge of how it was generated.

Study staff who interact with participants will be blinded to group membership until after the brief counseling session. They will not be informed of group membership until it is time to reveal it to the participants. Participants will not be blinded to group membership because there is no way to institute the intervention without revealing group membership.

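### The primary group × time ANOVA is valid, but it does not adjust for the day-7 dlPFC contrast or the randomisation strata; adjusting would cost almost nothing, for a gain the article does not let one fix

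*Protocol article*

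**What the plan says.** Analysis plan, Aim 1: the dlPFC percentage signal change for negative versus positive smoke trials is computed for each participant at each scan and "entered into a two-way mixed-effects ANOVA model using the group" by time interaction. Group and time are the only terms named.

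Power and sample size: the calculation uses a "two-sided two-sample" t-test. The outcome is pre-to-post change, as the control assumption shows: "Assuming the no practice group will have a mean of 0 change in brain activation between day 7 and day 21". The conservative inputs are stated as "the effect sizes are (0.0991/0.1415) = 0.70 and (0.2037/0.1889) = 1.08", and the result is that "40 per group provides 79% and > 99% power for dlPFC and vmPFC, respectively", at a Bonferroni-corrected two-sided alpha of 0.025.

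Randomization and blinding: "Groups will be stratified on gender and marijuana use to prevent these variables from confounding treatment effects", with separate blocked sequences for the four strata. In the Analysis plan these two variables appear only under the exploratory Aim 3.

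**The concern.** A change score gives the day-7 scan a fixed coefficient of 1, whatever its actual relation to the day-21 scan. Where the two are less than perfectly correlated, measurement noise in the first scan passes into the outcome. A chance difference between arms on day 7 also partly re-enters the comparison through regression to the mean. A regression on the day-7 value estimates the coefficient from the data instead.

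Allocation is stratified on two factors that the primary model leaves out, so design and analysis do not match.

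What is at stake is precision. The stated 79% lies just under the 80% benchmark that the same section uses, and it counts 40 analysable participants per arm, which is everyone randomised (N = 80). The Design justification section limits scanning to two sessions because of burden and resources, so fuller use of the first scan is the cheapest precision available.

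**Working it through.** **Inputs from the article.** n = 40 per arm; two-sided alpha 0.05/2 = 0.025; d = 0.0991/0.1415 = 0.70 on the change scale. **Not in the article, so assumed and varied:** the pre-post correlation ρ of the dlPFC contrast, and the ratio k = SD_post/SD_pre.

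**1. The plan's own figure.** Noncentral t, 78 degrees of freedom, noncentrality 0.70 × √(40/2) = 3.13: power 79.9%, against 79% stated. For vmPFC, d = 1.08 gives 99.4%, against > 99% stated. Both reproduce.

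**2. Same test.** With two time points and complete pairs, the interaction F equals the squared t on change scores. On one simulated data set both were 4.0343. The power calculation and the planned analysis therefore agree.

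**3. Error variances.**

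- Change score: SD_pre² + SD_post² − 2ρ·SD_pre·SD_post
- Baseline-adjusted (ANCOVA) residual: SD_post²(1 − ρ²)
- Difference: SD_pre² − 2ρ·SD_pre·SD_post + ρ²·SD_post² = (SD_pre − ρ·SD_post)² ≥ 0

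With k = 1 the ratio of ANCOVA to change-score variance is (1 + ρ)/2. For general k it is k²(1 − ρ²)/(1 + k² − 2ρk). For the same raw effect, d becomes 0.70/√ratio.

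**4. Power with baseline adjustment** (40 per arm, alpha 0.025, 77 degrees of freedom; planned test 79.9%):

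| k | ρ | variance ratio | d | power |
|---|---|---|---|---|
| 1.0 | 0.2 | 0.600 | 0.904 | 95.9% |
| 1.0 | 0.5 | 0.750 | 0.808 | 90.6% |
| 1.0 | 0.7 | 0.850 | 0.759 | 86.4% |
| 1.0 | 0.9 | 0.950 | 0.718 | 82.1% |
| 1.3 | 0.5 | 1.2675/1.39 = 0.912 | 0.733 | 83.7% |
| 1.3 | 0.7 | 0.8619/0.87 = 0.991 | 0.703 | 80.3% |
| 0.8 | 0.5 | 0.48/0.84 = 0.571 | 0.926 | 96.7% |
| 0.8 | 0.7 | 0.3264/0.52 = 0.628 | 0.884 | 95.0% |

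Simulation with 20,000 trials per ρ at k = 1, change score against ANCOVA: 80.2% against 90.2% at ρ = 0.5, and 79.8% against 86.0% at ρ = 0.7. The small shortfall from the table is expected, because the table ignores the slight extra variance from chance baseline differences.

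The gain vanishes where ρ = 1/k. At k = 1 that is ρ = 1; at k = 1.3 it is ρ = 1/1.3 = 0.77.

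**5. Strata.** A stable effect of gender or marijuana use on the level of activation adds the same amount to both scans and cancels in the difference. Only an effect on change (or, in the adjusted model, on the day-21 value given day 7) remains in the error. If the strata explain a share R² of that variance, d is divided by √(1 − R²):

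- Added to the change-score model: 79.9% at R² = 0, 82.0% at 5%, 84.2% at 10%.
- Added to ANCOVA at k = 1, ρ = 0.5: 90.5%, 92.0% and 93.4%.

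**The case against.** The strongest reply is that nothing here is wrong. The planned test is unbiased under randomisation, answers the stated hypothesis about pre-to-post increases, and agrees with the power calculation. That stands, and it limits the point to lost precision.

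A reader might infer more in several ways, and the article does not support these readings:

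- *That omitting the strata makes the planned standard errors too wide.* Stable stratum effects cancel in a group × time test. No effect on change is shown for marijuana use, and for gender there is only a hypothesis, under Other objectives.
- *That the analysis contradicts the randomisation section.* That section says stratification is there to prevent confounding. Stratified allocation serves that purpose by design, and the section promises no adjustment.
- *That power would rise to about 90% or more.* This needs equal SDs at the two scans and a moderate or low ρ. The article assumes equal variance between groups, not between time points.
- *That the adjusted model would keep participants whom the planned one loses.* A mixed-effects ANOVA fitted by likelihood may already keep those with one scan.
- *That baseline imbalance biases the planned test.* Change scores subtract baseline. What remains is regression to the mean given an imbalance, which averages out over randomisations.

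One further caveat stands. The preprocessing section takes the primary outcome from dlPFC clusters that pass thresholding, whereas the power figures here and in the plan assume a fixed outcome. Changing the final model does not touch that selection step.

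It can also be said that covariates are often left to an analysis plan. Here, however, the article names the primary model and its terms.

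**Conclusion.** The point holds as a recommendation on efficiency. The Aim 1 test is valid and its 79% is correct, but it leaves available precision unused.

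The direction is secure, since baseline adjustment never has the larger residual variance; its one extra degree of freedom costs under 0.1 point of power here. The size is not secure. For the planned raw effect at alpha 0.025, the gain over 79.9% runs from about 0.4 points (k = 1.3, ρ = 0.7) to about 17 points (k = 0.8, ρ = 0.5) across the cases shown. With equal SDs it is about 16 points at ρ = 0.2, 11 at 0.5, 6.5 at 0.7 and 2 at 0.9. All of this rests on assumed values of ρ and k, on 40 complete pairs per arm, and on a fixed dlPFC outcome.

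In the change-score model the strata are worth about 2 to 4 points if they explain 5–10% of the variance in change, and about nothing otherwise. The firmer reason to include them is agreement with the stratified allocation.

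**What to change.** Make the primary Aim 1 analysis a linear model of the day-21 dlPFC contrast on group, day-7 dlPFC contrast, gender and marijuana use, with the test on group. Keep the unadjusted group × time ANOVA as a sensitivity analysis. Report ρ and both SDs with the results so that the gain can be seen.

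The cost is a change of wording and about three degrees of freedom (78 to 75). Both scans and both stratification factors are already collected, so no new data are needed. The change should be fixed before outcomes are examined by group.

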#### Self-report assessments

##### Smoking characteristics

The Fagerström Test for Nicotine Dependence [42] will assess nicotine dependence. Items from the COMMIT Smoking Prevalence Survey [43] will assess smoking history such as tobacco use (cigarettes per day (CPD) and other tobacco use), age when first smoked, and quitting/relapse history. Because neural responses may be influenced by motivation to quit, we will assess this by asking: “How motivated are you to quit smoking?” on a scale from 0 to 10.

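### Aim 2 words an unadjusted Pearson correlation within the practice arm as the effect of adherence, and no planned analysis adjusts it for dependence, motivation or sex

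*Protocol article*

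**What the plan says.** The opening of the Analysis plan words the aim causally: "The second aim is to determine the effect of adherence to the practice regimen on changes in brain activation in cognitive control regions". The Aim 2 paragraph repeats this as identifying an impact. It then fixes the analysis set, "Using only participants from the practice group", and the method, "we will calculate Pearson correlations between differences in brain activation from the negative smoke and positive smoke conditions and amount of practice completed". It names no covariate.

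Other sections bear on this:

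- **Secondary objective** states the same question more weakly: "the secondary objective is to examine the association between the amount of practice" and dlPFC change. The last paragraph of the Background also speaks of associations.
- **Other objectives** hypothesises that practice-related increases "are expected to be greatest among more dependent and less motivated smokers as well as women".
- **Smoking characteristics** introduces the 0–10 motivation item with "Because neural responses may be influenced by motivation to quit, we will assess this by asking", and lists the Fagerström test. Gender is recorded at the consent appointment.
- **Design justification** notes: "Time to first cigarette of the day is also used as a proxy for level of nicotine dependence".
- **Practice group** provides for the schedule to be extended or cut back when a participant reports the lowest or highest difficulty.
- **Aim 3 (exploratory)** has a multiple regression for brain change that lists gender, motivation, dependence and other traits, but not amount of practice.

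**The concern.** Randomisation protects the comparison between arms. It gives no protection to a comparison, within one arm, of people who delayed more with people who delayed less. How much a participant practises depends on that participant, and through the difficulty rule the assigned delay does too.

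The protocol names three traits that it expects to relate to the outcome of this correlation. If any of them also relates to practice, the Pearson coefficient mixes the effect of practising with differences between people. A practice effect could then be masked, or one could appear where none exists. The causal wording would lead readers to take the coefficient as a dose-response effect. Aim 3 does not fill the gap, because amount of practice is not among its listed terms.

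**Working it through.** **The plan's own figures.** The protocol gives no power or effect size for Aim 2. Its Aim 1 figures are not in dispute: a noncentral t calculation with 40 per group and two-sided 0.025 gives 79.9% for d = 0.70 and 99.4% for d = 1.08, against the stated 79% and > 99%.

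**Inputs.** n = 40 is half of N = 80. Everything else is assumed, because the documents give no correlation of any trait with practice or with dlPFC change: two-sided 0.05, a standardised practice effect b = 0.4, and dependence D and motivation M independent of each other.

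**Model.** All variables are standardised: C = bP + gD − gM + e, with corr(P,D) = −a and corr(P,M) = +a. The signs are one choice among several.

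- Unadjusted r = b − 2ag.
- Residual variance s² = 1 − (b² + 2g² − 4abg).
- Partial r = b√(1 − 2a²) / √(b²(1 − 2a²) + s²).
- Power = Φ(atanh(r)√k − 1.96) + Φ(−atanh(r)√k − 1.96), with k = 37 unadjusted, 35 adjusted for D and M, and 34 when sex is added (charged as a degree of freedom only).

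**Example, a = g = 0.3.** Unadjusted r = 0.4 − 0.18 = 0.22. s² = 1 − (0.16 + 0.18 − 0.144) = 0.804. Partial r = 0.4√0.82 / √(0.1312 + 0.804) = 0.375.

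| a | g | unadjusted r | partial r | power, unadjusted | power, D and M | power, D, M and sex |
|---|---|---|---|---|---|---|
| 0 | 0.05 | 0.40 | 0.401 | 73.1% | 71.0% | 69.8% |
| 0.1 | 0.05 | 0.39 | 0.396 | 70.7% | 69.8% | 68.5% |
| 0.3 | 0.05 | 0.37 | 0.364 | 65.6% | 61.7% | 60.4% |
| 0 | 0.1 | 0.40 | 0.404 | 73.1% | 71.7% | 70.5% |
| 0.1 | 0.1 | 0.38 | 0.397 | 68.2% | 70.1% | 68.9% |
| 0.2 | 0.1 | 0.36 | 0.384 | 63.0% | 66.8% | 65.5% |
| 0.3 | 0.1 | 0.34 | 0.362 | 57.7% | 61.3% | 60.0% |
| 0.1 | 0.2 | 0.36 | 0.407 | 63.0% | 72.3% | 71.1% |
| 0.2 | 0.3 | 0.28 | 0.404 | 41.7% | 71.7% | 70.4% |
| 0.3 | 0.3 | 0.22 | 0.375 | 27.5% | 64.4% | 63.2% |

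With all three covariates the change runs from a loss of about 2 to 5 points at g = 0.05 to a gain of about 36 points at a = g = 0.3.

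**No practice effect (b = 0).** Unadjusted r = −2ag. At a = g = 0.3 this is −0.18, and the unadjusted test rejects 19.8% of the time instead of 5%. At a = 0.2, g = 0.3 it rejects 11.4%.

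**Opposite sign.** If the trait–practice links run the other way, the bias is +2ag. At a = g = 0.3 the unadjusted r becomes 0.4 + 0.18 = 0.58, which overstates the effect.

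**Simpler check, one confounder and no practice effect.** Spurious r is the product of the confounder's two correlations. Both at 0.3, 0.4 or 0.5 give r = 0.09, 0.16 or 0.25, and rejection of about 8.5%, 17% or 34%.

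**Price of adjusting.** The r detectable with 80% power is tanh((1.96 + 0.84)/√(n − 3 − q)) for q covariates: 0.43 at q = 0 and 0.45 at q = 3.

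**The case against.** The strongest reply is that the objective is already an association. The Background and the Secondary objective say so, and a Pearson correlation answers an association question. That stands for those sections. The Analysis plan nevertheless uses effect and impact wording for the same aim, so the text is inconsistent.

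A reader might go further and infer that the estimate is confounded, or that the bias must be negative and would hide a real dose-response. The documents do not support either reading. The expected role of the traits is a hypothesis, and the motivation remark says only that an influence is possible. Confounding also needs a link from trait to practice, and the protocol predicts no direction for one. The support is indirect: time to first cigarette as a dependence proxy, and the difficulty rule. The practice measure is scaled to each person's own first-to-second-cigarette interval, so baseline timing is not itself the measure.

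A reader might also infer that adjustment always pays. It does not: at g = 0.05 it loses power, and at g = 0.1 with a of 0.1 to 0.3 the gain is about 1 to 2.5 points once sex is included.

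The subgroup hypothesis can also be read as effect modification. Within a practice-only sample, modification of the practice-versus-no-practice effect does appear as a relation between trait and change. Main-effect adjustment would not, however, address a practice slope that differs by trait.

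Finally, covariates for a secondary analysis are often left to the SAP, which is not shown. Here the protocol names the method itself, so this concerns a stated choice and not a missing detail.

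**Conclusion.** The point holds as a weakness of a secondary analysis. Causal wording is attached to an unadjusted correlation with a non-randomised exposure, although the traits the protocol expects to matter are collected and no planned analysis adjusts practice for them. The estimate is open to confounding of unknown size and direction.

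The size depends wholly on the assumed a, g and b. At a = 0 there is no bias. The largest distortion examined is 0.18 on the correlation scale in the two-trait model and 0.25 in the one-confounder check. Aim 1 and its sample size are unaffected.

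**What to change.** Analyse Aim 2 with a partial correlation, or equivalently a linear regression of dlPFC change on amount of practice, adjusted for baseline Fagerström score, baseline 0–10 motivation and sex. Report the unadjusted Pearson correlation alongside it. Bring the Analysis plan into line with the association wording of the Background and the Secondary objective.

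All variables are already collected, so only the analysis text changes. The cost is three degrees of freedom out of about 40, and a small loss of power if the traits prove unrelated to practice or to change. Unmeasured differences between participants who practise more and less would remain, so association wording is needed even after adjustment.
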